### Previous results of folfiri plus cetuximab in first-line treatment of mCRC

Cetuximab is active and well tolerated in the first-line treatment of mCRC in association with fluoropyrimidine and irinotecan as demonstrated in the randomized, phase III, EMR 62202013 trial [22] in which the combination of cetuximab and irinotecan plus 5-fluorouracile infusion/folinic acid (FU/AF) was compared to CT only. The proportion of non-mutated KRAS patients was 64%. The response rate (RR: complete plus partial responses/number of evaluable patients) was 46.9% (CI: 42.9–51.0) in the CT/cetuximab arm, significantly higher (*p* = 0.0038) than that of the CT arm (38.7%; IC: 34.8–42.8). Odds ratios of subgroup analyses showed that, in the KRAS wt population, the RR of the cetuximab arm was significantly higher (59.3% vs 43.2%, odds ratio 1.91, 95% CI: 1.24–2.93). Furthermore, the association was able to improve PFS with a HR of 0.85 (IC: 0.726–0.998, *p* = 0.0479). The most common grade 3–4 toxicities in the combination arm were diarrhea (15.7% CT plus cetuximab vs 10.5% CT, *p* = 0.008) and those related to cetuximab infusion (2.5% CT plus cetuximab vs. 0% CT, *p* < 0.001). In the phase III, FIRE-3 study, mCRC patients carrying KRAS wt were randomized to folfiri plus cetuximab or folfiri plus bevacizumab first-line treatment [23]. The RR in the cetuximab group was 62.0% (95% CI: 56.2–67.5) and the median PFS was 10.0 months (95% CI, 8.8–10.8). Safety profile was not different from that previously described, with the most common grade 3–4 toxicities being haematologic (25%), skin reactions (26%), and diarrhoea (11%). The proportion of patients achieving an objective response did not significantly differ between the two groups.

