### Study design and statistical analyses

Sample size is based on a two-stage study design by Simon [29] with activity as primary end-point.

The null hypothesis of a not relevant response rate (40%) will be tested against an alternative response rate hypothesis of 70% with a one-tailed test. The test power is 95%, the alpha value of the I-type error is 5%. With these assumptions the sample for passing the first stage is 14 patients with > 6 objective responses. The final sample is 34 patients with > 18 objective responses to draw positive conclusions.

The populations considered for the analysis are described as follows. Safety Population (SP) is defined as all patients receiving at least one dose of treatment. Incorrect treatment or anticipation of the end of treatment are not reasons for exclusion from the SP. Efficacy Evaluable (EE) population is represented by patients who will receive at least one post-baseline assessment of the primary endpoint [28].

All patients who will receive at least one dose of treatment will be included in the descriptive statistics. The basic characteristics of the recruited patients will be reported for the categorical variables as total number and percentage and for the continuous variables as mean and standard deviation or median and interquartile range. Descriptive statistics of patients excluded from the SP and EE will also be carried out. Summary statistics on treatment will be compiled including information on dose changes, interruptions, non-compliance, reasons for protocol deviation, and treatment duration. The analysis on safety will be carried out on the SP. All the information necessary to identify the occurrence of adverse events will be used in the analysis and summarized through descriptive statistics. The confidence intervals will be calculated at 95%. Time-to-outcome will be described by Kaplan-Meier curves.

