#### Treatment phase

Clinical examination, evaluation of vital signs, blood count and clinical biochemistry will be performed at day 1 of each cycle before administration of folfiri/cetuximab (every 2 weeks). Cardiological evaluation, CEA, CA19.9 and assessment of response to treatment will be performed after 3 months of therapy start and thereafter every 3 months until progression.

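### The only efficacy population leaves out treated patients who are never scanned, so the reported response rate can only be biased upward; whether the type I error also suffers depends on what 14 and 34 count

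*Protocol article*

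**What the plan says.** The section on study design and statistical analyses of the protocol article defines two populations. The Safety Population (SP) is everyone who receives at least one dose, and the safety analysis is assigned to it. For efficacy: "Efficacy Evaluable (EE) population is represented by patients who will receive at least one post-baseline assessment of the primary endpoint". Patients excluded from either population are to be described. Nothing says that a treated patient without an assessment counts as a non-responder.

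The treatment-phase section fixes the timing: "assessment of response to treatment will be performed after 3 months of therapy start and thereafter every 3 months until progression". The section on response and toxicity assessment gives the same three-month schedule for imaging. The end-of-treatment section lists toxicity, progression and patient request as reasons for stopping, and provides for patients who die before the end-of-study visit.

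The decision rule is a Simon two-stage design. "The null hypothesis of a not relevant response rate (40%) will be tested" "against an alternative response rate hypothesis of 70% with a one-tailed test", with 95% power and 5% type I error. At stage 1, "the sample for passing the first stage is 14 patients with > 6 objective responses". At the end, "The final sample is 34 patients with > 18 objective responses to draw positive conclusions". Both sentences say patients, without saying whether treated or evaluable.

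**The concern.** Entry to the EE population is decided after treatment starts, and it is related to outcome. A patient lost before any scan cannot be a recorded responder, so removing that patient shrinks the denominator and leaves the numerator unchanged. The direction of the bias needs no assumption; only its size does.

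The trial has one arm, so no control group shares the bias. The hoped-for gain is 10 points over a historical rate of about 60%. The Discussion also relies on the two-stage design to limit the risk of an unexpected detrimental effect. If stage 1 were counted on evaluable patients only, early failures, who would be among the first signs of such an effect, would not count.

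**Working it through.** **Inputs from the article.** p0 = 0.40, p1 = 0.70, one-sided; n1 = 14, continue if more than 6 responses; n = 34, positive if more than 18 responses.

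**Input not in the article (assumption).** d = share of treated patients without any post-baseline assessment, all taken as non-responders. Values from 3% to 20% are shown.

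**Step 1. Reproduce the design.** With X1 ~ Bin(14, p) and X2 ~ Bin(20, p),

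P(positive | p) = sum over x = 7 to 14 of P(X1 = x) × P(X2 > 18 − x).

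- p = 0.40: 0.0385 (type I error); probability of stopping at stage 1: 0.692
- p = 0.70: 0.9507 (power)

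A full search over designs gives 6/14 and 18/34 as the Simon optimal design for these inputs. The stated design is correct.

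**Step 2. Reading A: 14 and 34 are treated patients, none replaced.** The rule is a count of responses. An unscanned patient adds no response, exactly as a non-responder would, so the type I error stays at 0.0385. Only the reported rate and its interval move. With 19 responders among 34 treated:

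| Unscanned | EE rate |
|---|---|
| 0 | 19/34 = 55.9% |
| 1 | 19/33 = 57.6% |
| 2 | 19/32 = 59.4% |
| 3 | 19/31 = 61.3% |

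The exact (Clopper-Pearson) 95% interval is 37.9 to 72.8 for 19/34 and 42.2 to 78.2 for 19/31. Three unscanned patients are enough to lift the lower limit above the 40% null.

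**Step 3. Reading B: 14 and 34 are evaluable patients**, so enrolment goes on until those numbers are assessed. The response rate in the EE population is then p/(1 − d). With a true all-treated rate of 40%, the formula of step 1 at that rate gives:

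| d | EE rate | P(positive) | P(pass stage 1) |
|---|---|---|---|
| 0 | 40.0% | 0.0385 | 0.308 |
| 3% | 41.2% | 0.052 | 0.342 |
| 5% | 42.1% | 0.064 | 0.367 |
| 10% | 44.4% | 0.106 | 0.437 |
| 15% | 47.1% | 0.172 | 0.517 |
| 20% | 50.0% | 0.271 | 0.605 |

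P(positive) passes 0.05 at d of about 2.5%. At d = 10%, a true 60% would be reported as 0.60/0.90 = 66.7%. A just-positive 19/34 would come from 34/0.90 = 37.8 treated patients, a rate of 50.3%.

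**Step 4. Power if all treated patients are counted.** If 70% is the true all-treated rate, power stays at 0.951. If 70% is meant as the rate among assessed patients, the all-treated rate is 0.70 × (1 − d):

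- d = 5%: 66.5%, power 0.895
- d = 10%: 63.0%, power 0.805

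**The case against.** A reader might infer that the plan breaks its 5% error at both looks. The article does not support that as a statement of fact. It has no replacement rule, it does not assign the Simon test to the EE population in so many words, and it says patients rather than evaluable patients. Under reading A the error is untouched. That the primary rate uses the EE population is an inference, though a natural one, since no other efficacy population is defined.

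A reader might also take "RR: complete plus partial responses/number of evaluable patients" as the trial's own definition of its endpoint. It stands in the account of a cited phase III trial. It can even be turned round: if the benchmark of about 60% is a rate per evaluable patient, an EE rate is the like-for-like comparison. The figures of step 3 take the 40% null as an all-treated rate, which the article does not state.

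Nor does every early failure or toxicity drop-out leave the EE population. Any one post-baseline assessment is enough for entry, so an unscheduled early scan showing progression keeps a patient in as a non-responder. Under the section on duration of therapy, toxicity from one drug leads to continuing the others, and assessments run until progression rather than until a drug is stopped. Eligibility requires a life expectancy above three months and ECOG 0 or 1, and excludes patients whose follow-up cannot be guaranteed, which should keep d low.

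Finally, replacement and missing-response rules may sit in the full protocol or analysis plan, and the article promises to describe excluded patients, so the exclusions would be visible.

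These points limit the size of the problem and make the error-rate claim conditional. They do not remove the bias. The EE definition is stated in the article rather than left to another document, and describing excluded patients does not put them back in the denominator.

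**Conclusion.** The point stands in two parts of different strength.

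- **Firm, on the natural reading that response is analysed in the EE population:** excluding treated patients who were never scanned can only raise the reported response rate. With 19 responders among 34 treated, three such patients move it by 5.4 points (55.9% to 61.3%).
- **Conditional:** the type I error exceeds 5% only if 14 and 34 mean evaluable patients, the 40% null is an all-treated rate, the unscanned are non-responders, and d is above about 2.5%. It is then 0.052 at d = 3% and 0.106 at d = 10%. The article gives no value for d. If 34 treated patients are counted without replacement, the error remains 0.0385.

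That the article leaves open which of these applies to its primary decision rule is itself a reason to settle the matter before the data are seen.

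**What to change.** State in the statistical section that the primary response rate and both Simon counts use the first 14 and the first 34 patients who receive at least one dose (the existing SP), that a patient without a post-baseline response assessment counts as a non-responder, and that such patients are not replaced. Keep the EE analysis as a sensitivity analysis. Say whether the 40% and 70% rates refer to all treated or to assessed patients.

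This takes a few sentences and changes neither treatment nor visits. The type I error is then 0.0385 whatever d is, if 40% is the all-treated rate. The reported rate may be slightly lower. If 70% was meant as the rate among assessed patients, power at 34 falls from 95% to about 90% (d = 5%) or 80% (d = 10%); the sponsor should either accept that or recalculate the sample size.

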### Eligibility criteria

The main inclusion criteria are: cytological or histological diagnosis of colorectal adenocarcinoma; KRAS, NRAS, BRAF wild-type; FcγRIIIa V/V genotype; stage IV; age < 75 years; at least 1 measurable lesion; ECOG Performance Status 0 or 1; life expectancy > 3 months; negative pregnancy test for all potentially childbearing women; written informed consent. The main exclusion criteria are as follows: previous systemic anti-tumor treatment (allowed treatment with capecitabine or fluorouracil and radiotherapy in the neoadjuvant setting of rectal tumors with therapy terminated at least 6 months before); presence of primary non-treated stenosing colorectal neoplasm; neutrophils < 2000/mm^3^ or platelets < 100.000/mm^3^ or hemoglobin < 9 g/dl; serum creatinine level > 1.5 times the maximum normal value; GOT and/or GPT > 5 times the maximum normal value and/or bilirubin level > 3 times the maximum normal value; previous malignant neoplasms (excluding basal or spinocellular cutaneous carcinoma or in situ carcinoma of the uterine cervix); active or uncontrolled infections; other concomitant uncontrolled diseases or conditions contraindicating the study drugs at clinician evaluation; presence of brain metastases; refusal or inability to provide informed consent; impossibility to guarantee follow-up.

### Therapeutic schedule

The therapeutic schedule [22, 23] is represented by cetuximab 400 mg/mq intravenously (iv) with a loading dose of 400 mg/mq at the first cycle followed by 250 mg/mq iv weekly. Cetuximab will be diluted in 500 ml of saline solution and administered by iv infusion in 90 min. The administration of irinotecan will precede that of cetuximab and will consist on a dose of 180 mg/mq diluted in 500 ml of saline solution and administered iv in 60 min. Fluorouracil (5-FU) will be administered at a dose of 400 mg/mq in slow iv bolus at half of lederfolin 200 mg/mq (diluted in 250 ml of saline solution) 2-h infusion. An elastomeric pump with 5-fu 2400 mg/mq in continuous 46 h-infusion will be adminstered after lederfolin. The therapeutic scheme just described is briefly indicated as folfiri/cetuximab. Only at the first administration of CT, irinotecan will not be administered (Fig. 1). This is a peculiar and innovative characteristic of the CIFRA study. ADCC occurs rapidly at the beginning of the therapy because it involves lympocytes subpopulatons (i.e. NK) that do not require immunological priming. Although immunomodulatory effects of irinotecan are not described, it is reasonable and biologically plausible that irinotecan-induced lymphopenia could interfere the ADCC phenomena.

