## Methods and design

CIFRA is a single arm, single center, open-label, phase II study, assessing the activity of cetuximab in combination with folfiri in FcγRIIIa V/V patients with KRAS, NRAS, BRAF wild type mCRC. It will be conducted at the academic hospital Istituto Nazionale Tumori di Napoli, IRCCS “G. Pascale” in Naples (Italy). The study includes also biomarkers’ analysis (cetuximab-mediated ADCC, TM characterization).

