### Objectives

The primary objective is to evaluate the role of the molecular and immunologic selection of patients on response to folfiri and cetuximab in patients with mCRC. The response will be evaluated according to Response Evaluation Criteria In Solid Tumors (RECIST) criteria, version 1.1 [28].

Secondary objectives are the safety, the responses’ duration, the progression-free (PFS) and overall survival (OS). Toxicity will be graded according to the Common Terminology Criteria for Adverse Events (CTCAE) of the National Cancer Institute, version 4.0, June 14, 2010. Response duration will be measured from the time of documented objective response (CR or PR) until documented tumor progression (see also “Response and toxicity assessment” section). PFS will be determined from the data of treatment start untill progression (defined according to RECIST), OS untill death from any cause. Tertiary and correlative objectives consist in exploratory studies of biological markers as predictors of outcome (see the “Tranlsational research” section).

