**Fig. 1 Fig1:**
[figure not shown]
Ideal timeline of CIFRA study

Atropine 0.25 mg sub cutis will be administered for the prevention of acute cholinergic events before irinotecan infusion. Premedication with *antihistamines at standard doses and* dexamethasone 4 mg will be applied before cetuximab infusion.

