## Discussion

The identification of predictive biomarkers characterizing the ideal treatment of mCRC patients is subject of intense investigation. RAS oncogenes in mCRC have not completely satisfied this unmet need since about 40% of patients with RAS wt mCRC dose not respond to anti-EGFR treatments. We previously reported in a series of 74 KRAS wt mCRC patients, genotypic frequencies of FcγRIIIa and FcγRIIa of 36% VV, 54% VF, 10% FF and 36% HH, 56% HR, 8% RR, respectively; interestingly, FcγRIIIa but not FcγRIIa polymorphisms were significantly associated with response to anti-EGFR-based therapy [20]. FcγRIIIa polymorphisms had also significant prognostic value for PFS [FcγRIIIa: median PFS 18.2 months in V/V patients (18 patients, 13 events) vs 17.3 months in V/F patients (26 patients, 25 events) vs 9.4 months in F/F patients (5 patients, 5 events); Log Rank test: *p* = 0.04] at univariate and multivariate analyses (HR: 2.35; CI: 1.37–4.01; *p* = 0.001) with grading and response to first-line chemotherapy. In another study, we described genotipic frequencies of FcγRIIa and IIIa in 96 consecutive mCRC patients and 148 control subjects and we analyzed the clinical impact of cetuximab-mediated ADCC in vitro from LAK patients-derived [21]. There were no statistically significant differences between the control and study groups in terms of genotypic frequencies. The incidence of FcγRIIIa V/V, V/F and F/F were: 28, 47 and 23%, respectively. Interstingly, the FcγRIIIa V/V and V/F genotypes were associated with higher cetuximab-mediated ADCC compared with F/F, median 27% (range: 0–76%) and 20% (0–57%) versus 9% (0–36%), respectively (*p* = 0.001). The response rate was higher in patients with the FcγRIIIa V allele (*V/V and V/F* genotypes) compared with the F/F genotype (*p* = 0.025) as well as the PFS of patients with FcγRIIIa V/V and V/F was significantly longer than that of patients with F/F (10.8 vs. 5.1 months respectively, *p* = 0.05, Log Rank test). The extent of in vitro cetuximab-mediated ADCC was significantly correlated with cetuximab clinical response (30% in responders vs 8% in non-responders patients, *p* = 0.020; ANOVA test). These observations prompted us to prospectively design the CIFRA trial, which is an investigator initiated phase II study to verify a superior activity of folfiri/cetuximab of 70% (+ 10% of that previously described) in mCRC patients selected on a genetic polymorphism of FcγRIIIa. The risk of a possible unexpected detrimental effect in this selected population is reduced in CIFRA study by the two-stage design that will stop the enrollment early if the first condition of acceptable activity is not met.

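### The primary objective credits response to patient selection, but every patient also gets an irinotecan-free first administration that the benchmark trials are not described as using, so the claim should cover both together

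*Protocol article*

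**What the plan says.** - **Objective.** In the Objectives section, the primary objective is to "evaluate the role of the molecular and immunologic selection of patients on response to folfiri and cetuximab".
- **Aim against a benchmark.** The section on the current therapeutic context and CIFRA hypothesis expects a higher response rate in V/V patients than the roughly 60% of previous trials. It adds that the results could settle for good the role of ADCC and FcγR polymorphisms in cetuximab activity. The Discussion says the trial was designed "to verify a superior activity of folfiri/cetuximab of 70% (+ 10% of that previously described) in mCRC patients selected on a genetic polymorphism".
- **Benchmark trials.** The section on previous results gives response rates of 59.3% (KRAS wild-type subgroup of EMR 62202013) and 62.0% (FIRE-3). The regimens are described as cetuximab with irinotecan and 5-FU/folinic acid, and as folfiri plus cetuximab. Neither description mentions a first cycle without irinotecan.
- **Regimen here.** The Therapeutic schedule section cites these two trials as its source, then states: "Only at the first administration of CT, irinotecan will not be administered". It continues: "This is a peculiar and innovative characteristic of the CIFRA study". The reason given is that ADCC starts early and that irinotecan-induced lymphopenia might interfere with it.
- **Design and test.** Methods and design: "CIFRA is a single arm, single center, open-label, phase II study". The statistical section sets a "null hypothesis of a not relevant response rate (40%) will be tested against an alternative response rate hypothesis of 70" per cent, "with a one-tailed test".

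**The concern.** Two deliberate choices, genotype selection and the irinotecan-free start, are aimed at the same mechanism and given to every patient. Only the first appears in the objective, the hypothesis and the Discussion. A response rate above about 60% could reflect selection, the altered first administration, or both. A rate at or below it could reflect a lack of selection effect or a loss from less early irinotecan. Followed as written, the plan would credit selection with a result that the data cannot assign to it. What is at stake is the conclusion the trial may draw and any later trial built on it, not the validity of the test.

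**Working it through.** **1. Reproduce the stated design.** Inputs from the statistical section: null rate 0.40, alternative 0.70, one-sided alpha 5%, power 95%; continue if more than 6 of 14 respond; positive if more than 18 of 34 respond.

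P(positive | p) = Σ over x = 7 to 14 of Bin(x; 14, p) × P(Y ≥ 19 − x), with Y ~ Bin(20, p).

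- p = 0.40: 0.0385, within the 5% limit.
- p = 0.70: 0.9507.
- Probability of stopping early under the null: 0.6925. Expected sample size under the null: 14 + (1 − 0.6925) × 20 = 20.15.

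A search of Simon designs up to n = 42 returns this rule as the optimal design for these inputs. Neither the 60% benchmark nor the irinotecan omission enters it.

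**2. What the rule can and cannot distinguish.** The documents give no effect for the omission, so the shifts below are assumptions. They are added to a starting rate of 60%.

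| Selection effect | Regimen effect | True rate | P(positive) |
|---|---|---|---|
| 0 | 0 | 60% | 0.699 |
| +10 | 0 | 70% | 0.951 |
| 0 | +10 | 70% | 0.951 |
| +5 | +5 | 70% | 0.951 |
| 0 | +5 | 65% | 0.861 |
| +10 | −5 | 65% | 0.861 |
| 0 | −5 | 55% | 0.483 |

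Rows with the same true rate are identical to the trial. A ten-point gain from selection and a ten-point gain from the regimen give the same 0.951. The data show only the sum.

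**3. Size of the departure in exposure.** Cycles are two-weekly, and response is assessed at 3 months and every 3 months thereafter (Treatment phase).

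- First scan at 12 to 13 weeks: 6 to 7 cycles, one irinotecan dose omitted. 1/7 = 14% to 1/6 = 17%.
- Second scan at 24 to 26 weeks: 12 to 13 cycles. 1/13 = 7.7% to 1/12 = 8.3%.

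The share falls at each later scan, and response is not restricted to the first one.

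**4. Side by side.** The objective and the Discussion name one factor (selection). The schedule section introduces a second (irinotecan-free start) and calls it innovative. The benchmark descriptions contain neither V/V selection nor the modified start. No section treats the second factor as a possible explanation of a difference from the benchmark.

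**The case against.** The strongest reply has four parts.

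- **The formal test is sound.** It uses 40% against 70%, not 60%, and its error rates reproduce. Methods and design speaks of assessing activity in V/V patients, and the statistical section names activity as the endpoint. This stands: the trial can say whether this treatment is active in these patients. It does not cover the objective and the Discussion, which claim more.
- **The single arm is the larger limit.** With no non-V/V group, a selection effect could not be isolated even with an unmodified regimen. This also stands. A reader might infer that giving irinotecan from the first cycle would make the objective answerable; it would not. The omission adds a treatment difference to an existing limit on attribution.
- **The change is disclosed.** The schedule section states it openly and gives a reason, so the article cannot be said to conceal it. What is missing is its place in the objective and the conclusion.
- **Only one dose is involved.** This is true, and the 14-17% applies only up to the first scan. But the protocol's own rationale makes the start of therapy important for ADCC, so the first administration cannot be set aside when the result is attributed.

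A reader might also infer that the rationale contradicts itself, because 5-FU is kept in the first cycle and "dexamethasone 4 mg will be applied before cetuximab infusion". The documents do not support this: nowhere do they say that either drug impairs ADCC, and the rationale concerns irinotecan alone. Nor would lymphocyte counts across the first cycles test the rationale. All patients receive the same sequence, so irinotecan is mixed with cumulative 5-FU, weekly cetuximab and time.

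**Conclusion.** The point holds as one of attribution. The objective and stated aim credit selection, while the plan delivers selection together with a modified first administration, read against trials not described as using it. The size and direction of any regimen effect are unknown. The shifts of −5, +5 and +10 points are illustrations, set against a hypothesised difference of ten points.

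A reader might go further and infer that the primary test is invalid or the trial uninterpretable. The documents do not support that: alpha is 0.0385, power is 0.951, and no sample-size figure depends on this point. The conclusion rests on the article's own description of the benchmark regimens; the cited reports were not consulted. No view is taken on which irinotecan schedule is right.

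**What to change.** 1. Restate the primary objective and the permitted conclusion as the activity, meaning response rate tested against the 40% null, of folfiri/cetuximab with an irinotecan-free first administration in FcγRIIIa V/V, KRAS/NRAS/BRAF wild-type patients.
2. State that any difference from the benchmark of about 60% cannot be credited to selection alone, since the trial has one arm and the first administration also differs from the benchmark regimens as described.
3. Remove the claim in the hypothesis section that the results could settle the role of ADCC and FcγR polymorphisms, and bring the wording of the Discussion into line.

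Cost: text changes only, with no change to sample size, decision rule, treatment or visits. The downside is a narrower claim.
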